### Participating Physicians

Participating trial physicians are employees of the Multidisciplinary Pain Centre, Department of Anaesthesiology, University of Munich, Germany. Their average qualification is at least equal to a 3^rd ^year resident in the field of anaesthesiology and specialised pain medicine. They contributed to all medical duties.

### Interventions

Patients are randomly allocated to either the preemptive or the postoperative treatment group. Preemptive group patients get etoricoxib 120 mg p.o. prior to surgery (day 0). After surgical intervention, depending on their respective allocation, patients receive either etoricoxib 120 mg p.o. or placebo for the next three postoperative days (day 1-3). Postoperative group patients get placebo prior to surgery and continue afterwards with either placebo or etoricoxib 120 mg p.o. for three postoperative days (2 × 2 factorial study design, Figure 1). All patients will receive standardised morphine (patient controlled analgesia PCA; bolus 2 mg; interval 10 min; max dosage 30 mg/4 h). Patients, study physicians and contributing hospital staff are blinded regarding the treatment group allocation.

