**Figure 1 F1:**
[figure not shown]
**Study Design**. Patients are randomly allocated to either the preemptive or the postoperative treatment group. Preemptive group patients get etoricoxib 120 mg p.o. prior to surgery (day 0, preoperative). After surgical intervention, depending on their respective allocation, patients receive either etoricoxib 120 mg p.o. or placebo for the next three postoperative days (day 1-2-3, postoperative). Postoperative group patients get placebo prior to surgery and continue afterwards with either placebo or etoricoxib 120 mg p.o. for three postoperative days (2 × 2 factorial study design). The listed outcome measures will be assessed at the marked time points respectively.

We conducted a 2 × 2 factorial-armed study which should prove the superiority of preemptive versus postoperative etoricoxib. The study was based on the moderate effective size of pre-emptive etoricoxib vs. post-operative etoricoxib in the reduction of the 48 hour cumulative morphine consumption. A sample size of approximately 60 patients in the two arms (i.e. 30 patients in each of the four arms) is anticipated taking a drop out rate of 10% into account (this is a conservative estimate based on the dropped out rate of 4% in the study by Sinatra et al. [19]). With this sample size we would permit a type I error of alpha = .05, and with the alternate hypothesis, the null hypothesis would be retained with a type II error of beta = .2 (i.e. power of 80%).

The calculation of the effective size is based on the data of Sinatra et al. [19]. The authors found a mean reduction of cumulative morphine consumption of 23 mg in the treatment group (total morphine dose 45 mg, SD 14) compared to the placebo group (total morphine dose 68 mg, SD 25).

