### Outcome measures

#### Main outcome measure

The cumulative morphine consumption (mg) within the first 48 hours after surgery (PCA)

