## Etoricoxib

Several COX-2-inhibitors have been shown to be effective treating postoperative pain [31-33]. Data for the use of etoricoxib seem to be promising; however, existing results describing preemptive and postoperative effects remain heterogeneous [34-36]. Etoricoxib is a COX-2-selective NSAID which is approached for treatment of osteoarthritis, rheumatoid arthritis, acute gouty arthritis and Morbus Bechterew. Numerous studies indicated that etoricoxib has similar efficacy as traditional, unselective NSAIDs have. It does not seem to elevate the risk of severe side effects, i.e. in special vascular events [29,37]. The rates of thrombotic cardiovascular events in 34.000 patients with arthritis on etoricoxib were similar to those in patients with long-term use of diclofenac [29]. Ex vivo whole-blood assays after multiple oral doses of etoricoxib showed no important effects on bleeding time or platelet aggregation [38]. Consequently, these drugs do not carry the risk of blocking surgical interventions.

Additionally, etoricoxib demonstrated superior safety in gastrointestinal toxicity due to its high selective COX-2 inhibition that is observed with its use. Other NSAID-associated effects, including renal adverse effects, appear to be similar to those of other traditional NSAIDs [20].

The pharmacokinetic evaluation of etoricoxib indicates a moderate rate of absorption and a t1/2 of approximately 20 hours that enables once-daily dosing [20].

We have chosen etoricoxib as verum treatment due to the presented pharmacologic properties such as our own clinical experience dealing with. Drug approval for peri- and postoperative setting has not yet been authorised.

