## Conclusion

This study is a large-scale randomised placebo-controlled trial to evaluate the efficacy of COX-2-inhibitors in preemptive and postsurgical pain therapy. It can be expected to provide new valuable information on clinical and pathophysiological effects in postoperative pain, i.e. a) the analgetic effectiveness of preemptive analgesia and b) its relation to e.g. sensoric perception or genetical predisposition as possible factors leading to persistent (chronic) pain.

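### The preoperative factor tests one extra etoricoxib dose against placebo, so it cannot show that preemptive dosing is superior to postoperative dosing

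*Protocol article*

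**What the plan says.** All references are to the protocol article.

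- **Schedule (Interventions).** "Preemptive group patients get etoricoxib 120 mg p.o. prior to surgery (day 0"). Afterwards, "patients receive either etoricoxib 120 mg p.o. or placebo for the next three postoperative days (day 1-3"). For the other group, "Postoperative group patients get placebo prior to surgery and continue afterwards with either placebo or etoricoxib 120 mg p.o. for three postoperative days". That last sentence names no day; the days come from the sentence before it and from the Figure 1 legend ("for the next three postoperative days (day 1-2-3, postoperative"). No arm is described as receiving active drug after surgery on day 0, and the hour of the first postoperative tablet is not given.
- **Endpoint (Main outcome measure).** "The cumulative morphine consumption (mg) within the first 48 hours after surgery (PCA").
- **Drug (Etoricoxib).** The article gives "a t1/2 of approximately 20 hours that enables once-daily dosing".
- **Aim, stated two ways.** The Abstract asks whether preemptive analgesia does better than placebo. The sample-size text after the Figure 1 legend says the trial should show preemptive etoricoxib to be superior to postoperative etoricoxib.
- **Analysis (Data Analysis).** A 2 × 2 ANOVA, with one factor labelled by when the medication is taken.
- **Promise (Conclusion).** Information on "the analgetic effectiveness of preemptive analgesia".

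**The concern.** A claim that preemptive dosing beats postoperative dosing is a claim about timing. To test it, patients would need comparable drug exposure that starts before surgery in one arm and after it in another. Here the preoperative factor adds a dose, and that dose is still present during the hours in which the primary endpoint is counted. A lower 48 h morphine total in the preoperative-active arms could come from dosing before the noxious stimulus, which is the concept set out in the Background. It could equally come from having an analgesic on board when the comparison arms have less or none. Both lower the total, and a single 48 h sum cannot tell them apart. At stake is what a positive primary result may be said to show.

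**Working it through.** The article gives no figure for this point, so there is none to reproduce. The check is a dose count, then an exposure sketch, then an illustration in mg. E is etoricoxib and P is placebo; the first letter is preoperative, the second postoperative.

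**1. Active doses per arm** (Interventions: one on day 0, three on days 1-3)

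| Arm | Day 0 | Days 1-3 | Total |
|---|---|---|---|
| E/E | 1 | 3 | 4 |
| P/E | 0 | 3 | 3 |
| E/P | 1 | 0 | 1 |
| P/P | 0 | 0 | 0 |

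- Preoperative contrast with active postoperative drug: 4 vs 3.
- Preoperative contrast with postoperative placebo: 1 vs 0.
- Main effect: (4 + 1)/2 = 2.5 vs (3 + 0)/2 = 1.5, again one extra dose. Half of the so-called postoperative group never receives etoricoxib.
- E/P vs P/E, the cells nearest to a pre-versus-post comparison: 1 vs 3 doses.

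**2. How long the extra dose lasts.** First-order decay with the stated half-life, absorption ignored: fraction left = 0.5^(t/20).

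- 12 h: 0.66
- 24 h: 0.44
- 48 h: 0.19

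**3. Exposure after surgery.** Assumptions: one compartment, instant absorption, unit dose, preoperative tablet 2 h before the end of surgery, postoperative tablets 24 h apart. With k = ln 2/20 = 0.0347 per h, exposure from the preoperative tablet between the end of surgery and time f is (e^(−2k) − e^(−(f+2)k))/k.

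| First postoperative dose | Exposure before it: preoperative E vs P | 0-48 h: E/E | P/E | E/P |
|---|---|---|---|---|
| 2 h | 1.8 vs 0 | 60.2 | 38.4 | 21.8 |
| 12 h | 9.2 vs 0 | 52.2 | 30.4 | 21.8 |
| 18 h | 12.5 vs 0 | 45.9 | 24.1 | 21.8 |
| 24 h | 15.2 vs 0 | 38.1 | 16.3 | 21.8 |

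(P/P is 0 throughout.) An early first postoperative dose nearly closes the uncovered gap. The extra exposure over 48 h (E/E minus P/E, or E/P minus P/P) is nevertheless 21.8 in every row. E/P vs P/E is not an equal-exposure comparison either: P/E has more exposure at 2, 12 and 18 h and less at 24 h.

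**4. What this could mean in mg.** The article cites a 23 mg reduction against placebo (45 mg, SD 14, vs 68 mg, SD 25). Assume that this accrues evenly over 48 h purely from drug on board: 23/48 = 0.479 mg per h. Assume also that the preoperative tablet contributes only in the hours before the first postoperative dose, and that timing has no benefit at all. Pooled SD = √((14² + 25²)/2) = 20.26 mg. Evaluable per factor level = 60 × 0.9 = 54. Standard error = 20.26 × √(2/54) = 3.90 mg. Probability of significance = Φ(difference/3.90 − 1.96), two-sided 5% (the article does not state sidedness).

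| First postoperative dose | Apparent preoperative effect | Chance of significance |
|---|---|---|
| 12 h | 0.479 × 12 = 5.8 mg | 31% |
| 18 h | 0.479 × 18 = 8.6 mg | 60% |
| 24 h | 0.479 × 24 = 11.5 mg | 84% |

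The same figure is used in both postoperative strata. In E/P vs P/P no later active dose ends the gap, so for that stratum the figure is, if anything, low.

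**The case against.** The strongest reply is that the trial does answer a valid question. Preoperative etoricoxib against preoperative placebo, randomised and balanced over the postoperative factor, is unbiased for adding a preoperative dose. That is the objective in the Abstract. The Background calls the definition of preemptive analgesia controversial and uses a broad concept, namely that treatment begins before the stimulus. Drug still present after surgery is part of the randomised intervention and is not a source of bias. All of this stands.

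A reader might therefore go too far in three ways:

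- **That the trial can conclude nothing about preemptive efficacy.** The documents do not support this. Under the Abstract's objective and the broad concept, the contrast is informative. What it cannot support is superiority over postoperative dosing, or an effect of timing as such.
- **That for about the first 24 h the comparison is simply drug against nothing.** This needs the hour of the first postoperative dose, which is not given. A day-1 tablet could fall well before 24 h after surgery, hence the range above.
- **That E/E vs P/E over 24-48 h would isolate a preemptive effect.** It would not. With doses 24 h apart, E/E holds 1 + 0.44 = 1.44 dose units after the first postoperative tablet against 1.00 in P/E. The extra dose is still there, with half the patients (about 27 vs 27) and 80% power only at about 0.78 SD.

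It can also be said that splitting the 48 h total is a matter for the analysis plan, which is not shown. That is fair, and the lack of such a split is not part of this point.

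**Conclusion.** The point holds as a mismatch between claim and design. Under the stated schedule the preoperative factor estimates the effect of one extra active dose over placebo (4 vs 3, 1 vs 0), and no pair of arms compares equal exposure before and after surgery. The superiority claim in the sample-size text and the timing label in Data Analysis therefore promise something that the 0-48 h total cannot deliver.

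The dose count rests on the text alone. The size in mg does not: 5.8 to 11.5 mg, with a 31% to 84% chance of significance, depends on even accrual of the cited 23 mg, on the assumed hour of the first postoperative dose (12 to 24 h), and on the pooled SD of the cited study. It shows that a significant result without any timing benefit is plausible; it does not predict one. The estimate of adding a preoperative dose remains valid.

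**What to change.** Nothing here asks for a change in dosing.

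1. Reconcile the Abstract, the sample-size text and Data Analysis. The primary hypothesis, the ANOVA factor label and the conclusion should all refer to the effect of adding a preoperative etoricoxib dose, versus placebo, on 48 h morphine use.
2. Remove the claim that preemptive timing is superior to postoperative timing, and read the promise in the Conclusion in the same restricted sense.
3. Optionally, report the PCA totals for 0-24 h and 24-48 h descriptively. Do not present E/E vs P/E in the later window as a preemptive effect.

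The cost is rewording and a narrower primary claim. The randomisation, the endpoint and the 2 × 2 analysis stay as they are.

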### Ethics

The study is performed according to the principles of the Declaration of Helsinki (Version Edinburg 2000, cf. http://www.wma.net/en/30publications/10policies/b3/index.html) and according to common guidelines for clinical trials (ICH-GCP). The protocols have been approved by the Ethics Committee, University of Munich and the national component authority (German Federal Drug Administration [Bundesinstitut für Arzneimittel und Medizinprodukte BfArM]). Written informed consent is obtained from all patients.

### Outcome measures

#### Main outcome measure

The cumulative morphine consumption (mg) within the first 48 hours after surgery (PCA)

#### Secondary outcome measure

- Baseline personal situation on the DGSS (German Society for the Study of Pain) validated pain questionnaire [24], comprising inter alia the German versions of questionnaires assessing demographic data, pain variables (e. g. pain sites, temporal characteristics, duration, intensity), pain associated symptoms, affective and sensory qualities of pain (adjective list by Geissner, SES), pain relieving and intensifying factors, previous pain treatment procedures, pain-related disability (Pain Disability Index), depression (Centre for Epidemiological Studies Depression Test CES-D), comorbid conditions, social factors (educational level, occupation, retirement status, compensation or litigation status, disability for work), health related quality of life (SF-36).

- Systematic quantitative sensory testing (QST). The detailed QST protocol including reference data is reported elsewhere [25]. In brief, the following testing procedures were performed:

a) **Thermal Testing **comprising cold and warm detection thresholds (CDT, WDT), paradoxical heat sensations (PHS) during the thermal sensory limen procedure (TSL) of alternating warm and cold stimuli and cold and heat pain thresholds (CPT, HPT);

b) **Mechanical Testing **comprising mechanical detection thresholds (MDT), mechanical pain thresholds (MPT), mechanical pain sensitivity (MPS), dynamic mechanical allodynia (DMA), the wind-up ratio (WUR), vibration detection thresholds (VDT) and pressure pain thresholds (PPT).

- Pain intensity (visual analogue scale)

- Overall morphine consumption

- Side effects (documentation according to ICH - GCP Guidelines)

- Genetic polymorphisms: the metabolic profile of etoricoxib involves cytochrome P450-dependent hydroxylation and oxidation as primary clearance pathways [26]. Different genotypes might either be the reason for individually different analgesic needs or be considered as a risk factor for side effects [27]. Similar mechanisms have been described for the use of opioids and so called multidrug resistance proteins (MDR) [28]. We therefore collected EDTA-blood samples from all patients to analyse the different expression of genotypes.

For time points please refer to Figure 1.

### Data Analysis

Descriptive analysis of the study population (including means, standard deviations, median and frequencies) will be made for all parameters.

Main outcome measures will be analysed with a 2 × 2 factorial ANOVA. Independent variables are time point of medication uptake and allocated study arm, dependent variable is the cumulative morphine consumption within 48 hours postoperatively.

Secondary outcome measures (QST, pain intensity) will be analysed equivalent, taking into account the test interval (repeated measurement ANOVA). ANOVA will be adjusted according to Bonferroni using t-test for post-hoc confirmation of significant alterations.

Ordinal scaled data will be analysed with Kruskal Wallis test confirming significance with chi2 test.

For analyses of associative coherence we will use Spearman's correlations coefficient, Wilcoxon-test or Kruskal Wallis test. All reports will be performed according intention-to treat analysis.

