**Design and Methods:**

The study is a 2 × 2 factorial armed, double blinded, bicentric, randomised placebo-controlled trial comparing (a) etoricoxib and (b) placebo in a pre- and postoperative setting. The total observation period is 6 months. According to a power analysis, 120 patients scheduled for abdominal or thoracic surgery will randomly be allocated to either the preemptive or the postoperative treatment group. These two groups are each divided into two arms. Preemptive group patients receive etoricoxib prior to surgery and either etoricoxib again or placebo postoperatively. Postoperative group patients receive placebo prior to surgery and either placebo again or etoricoxib after surgery (2 × 2 factorial study design). The Main Outcome Measure is the cumulative use of morphine within the first 48 hours after surgery (measured by patient controlled analgesia PCA). Secondary outcome parameters include a broad range of tests including sensoric perception and genetic polymorphisms.

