### Patients

For the included patients the following criteria must be met:

- Age ≥ 18 years

- Scheduled abdominal or thoracic surgery harming peritoneum or pleura

- ASA classification I or II according to the American Society of Anaesthesiologists

Main exclusion criteria are:

- Severe cardiac/pulmonary/renal or neurologic diseases

- ASA score > II

- Patients with insulin-dependent diabetes mellitus or other diseases influencing the peripheral sensibility (e.g. polyneuropathy, chronic pain syndromes)

- Regional blocks

- Continuous use of analgesics

- Pregnancy or lactation

- Uncontrolled hypertension

- Contraindications listed in the product information of etoricoxib, i.e. intolerance, ulcers or gastric bleeding, inflammatory bowel diseases, anaphylactic reactions

Information will be held on the vigil of surgery. If criteria are appropriate and patients want to participate, they give their written informed consent with sufficient time of consideration.

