## Quantitative sensory testing

Postoperative pain involves not only peripheral mechanisms, most notably the sensitization of nociceptors due to inflammation, but also secondary central mechanisms, including hyperexcitability of nociceptive neurons (i.e., central sensitization, [39,40]). These processes play a major role in postoperative pain, including spontaneous pain and allodynia or hyperalgesia. In particular, peripheral sensitization would explain the hyperalgesia observed at the incision site (primary hyperalgesia), whereas central sensitization would provide a major mechanism of secondary hyperalgesia at distant noninflammatory sites [41-43]; thus indicating a possible pathway for the occurrence of prevalent pain.

From a clinical perspective, preoperative measurement of sensoric perception may have some predictive value regarding postoperative pain and, therefore, may also predict perioperative analgesic requirement [44]. Martinez et al. showed that preoperative heat hyperalgesia directly correlated with postoperative morphine consumption after total knee arthroplasty [43]. These results are in agreement with those of previous studies on the prognostic value of preoperative pain for immediate postoperative pain intensity with other types of surgery [45,46]. Postoperative segmental secondary hyperalgesia was detected in patients undergoing different types of surgical interventions [47-49]. Several central and peripheral pathophysiological actions play a role in the development of acute and chronic postoperative pain. Quantitative sensory testing (QST) allows precise characterization of sensory deficits and painful symptoms and may offer additional information on the pathophysiology of postoperative pain. A follow-up sensory testing in our trial is performed six months after intervention. Therefore, we will be able to provide information regarding long-term sensitisation after surgery, too. Taken together, we will be able to evaluate possible predictive factors related to patients' individual sensoric perception that may influence the intensity of postoperative pain and analgesic consumption such as characteristics that might predict or prevent chronification.

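### The primary 2 × 2 ANOVA lists only treatment terms and gives up precision that prespecified adjustment for surgery type and baseline heat pain threshold could supply

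*Protocol article*

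**What the plan says.** - **Primary model (Data Analysis).** "Main outcome measures will be analysed with a 2 × 2 factorial ANOVA". The section then lists the independent variables: when the study drug is taken, and the arm allocated. The dependent variable is cumulative morphine over 48 hours. No baseline variable is listed.
- **Population (Patients).** Eligibility is "Scheduled abdominal or thoracic surgery harming peritoneum or pleura".
- **Prognostic argument (Quantitative sensory testing).** The article says preoperative sensory perception may predict perioperative analgesic requirement. It cites a study in which "preoperative heat hyperalgesia directly correlated with postoperative morphine consumption after total knee arthroplasty". Heat pain threshold is part of the test battery under Secondary outcome measure.
- **Centres.** The abstract describes a "double blinded, bicentric, randomised placebo-controlled trial". The Study Design paragraph under Patients and Methods does not repeat the word for two centres, and Participating Physicians names one department.
- **Sample size (Randomised treatment allocation, blinding and sample-size estimation).** "A sample size of approximately 60 patients in the two arms (i.e. 30 patients in each of the four arms) is anticipated", allowing for 10% dropout, with alpha 0.05 and 80% power. The section calls the effect moderate without a number. It also cites a 23 mg difference: 45 mg (SD 14) on treatment and 68 mg (SD 25) on placebo.

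**The concern.** Surgery type is known for every patient before randomisation and plausibly affects morphine use. By the article's own account, baseline heat pain sensitivity may also predict the kind of outcome that is primary here. The analysis section uses such predictors at most in association analyses (Spearman, Wilcoxon, Kruskal-Wallis). With neither variable in the primary model, any outcome variance they explain inflates the standard error of the treatment contrasts, and a chance imbalance in them is left in the estimate. What is at stake is the width of the confidence interval, and with it power. The validity of the test is not in question. The choice also has to be made in advance, because covariates added after unblinding invite doubts about selection.

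**Working it through.** **Inputs.** From the article: 60 per marginal group, 10% dropout (60 × 0.9 = 54 evaluable per group, 108 in all), alpha 0.05, power 80%, difference 23 mg, SDs 14 and 25. Assumed: two-sided testing, R² of 0.1 to 0.3, and d = 0.5 where stated.

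**Step 1: the article's own sample size.** Combined SD = √((14² + 25²)/2) = 20.26 mg, so d = 23/20.26 = 1.135. With n per group = 2(1.960 + 0.842)²/d²:
- Cited figures, SD 20.26: 13 per group, 15 with dropout.
- Cited difference with SD 25 (d = 0.92): 19 per group, 22 with dropout.
- Assumed d = 0.5: 63 per group, 70 with dropout.

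None of these gives 60. Solving backwards, 54 evaluable per group corresponds to d = 2.802 × √(2/54) ≈ 0.54.

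**Step 2: unadjusted power with 54 per group.**
- At 23 mg (d = 1.135, or 0.92 with SD 25): above 99%.
- At d ≈ 0.54: 80%, by construction.
- At assumed d = 0.5: noncentrality 0.5 × √(54/2) = 2.598. With 108 − 4 = 104 error degrees of freedom, the noncentral t gives 73%. The normal approximation gives 73.8%.

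**Step 3: effect of adjustment.** If the covariates explain a share R² of the within-cell variance, the residual SD is SD × √(1 − R²). Surgery type, heat pain threshold and, if used, centre leave 102 or 101 error degrees of freedom; the rounded results are the same for both. The mg columns use SD 20.26.

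| Assumed R² | √(1 − R²) | Fall in residual SD | Power at d = 0.5 | Difference detectable at 80% | 95% CI half-width |
|---|---|---|---|---|---|
| 0 | 1.000 | – | 73% | 11.0 mg | 7.7 mg |
| 0.1 | 0.949 | 5% | 77% | 10.5 mg | 7.3 mg |
| 0.2 | 0.894 | 11% | 82% | 9.9 mg | 6.9 mg |
| 0.3 | 0.837 | 16% | 87% | 9.2 mg | 6.5 mg |

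The half-width is t × SD × √(1 − R²) × √(2/54). At R² = 0.2 the gain equals having 54/0.8 ≈ 67 evaluable patients per group instead of 54.

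**Step 4: the contrast matters.** The table is for marginal groups of 54. If pre-emptive against postoperative etoricoxib is read as one cell against another (27 against 27), power at d = 0.5 by the normal approximation is 45% unadjusted and 59% at R² = 0.3. Reaching 80% would need R² of about 0.57.

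**The case against.** The strongest reply is that nothing here is an error. In a randomised trial the unadjusted factorial ANOVA is valid, and its type I error already allows for chance imbalance. That stands. It makes this a point about efficiency, not correctness.

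The second reply is that covariate lists are often left to a full protocol or analysis plan, neither of which is shown. This carries less weight, because the article does not stay silent: it names the primary model and lists its terms. Stratified randomisation is not described, but a condensed article does not allow the inference that there was none.

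The third reply is that the support for particular covariates is thin, and in part it is:
- The cited heat pain correlation comes from knee arthroplasty, and no strength is given.
- Figure 1, which holds the time points, is not shown, so preoperative testing of every patient cannot be confirmed.
- Two centres are mentioned only in the abstract.
- Age is nowhere presented as prognostic, so it is not proposed.

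Surgery type needs none of these caveats about availability.

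A reader might go further and infer that the trial delivers only 73% power and needs adjustment to reach 80%. The documents do not support this. The 73% follows from reading "moderate" as exactly d = 0.5. The only effect figures given yield over 99%, and the d of about 0.54 implied by 60 per group yields 80%. The 23 mg figure is not firm reassurance either, since it compares treatment with placebo while the stated aim is pre-emptive against postoperative etoricoxib. That mismatch is a separate question which adjustment does not settle.

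**Conclusion.** The point holds as an efficiency improvement. The stated primary model omits a known design feature (surgery type) and a baseline measure that the article itself argues may be prognostic, so it gives up whatever precision they carry. The amount is unknown. A 5% to 16% fall in residual SD rests on an assumed R² of 0.1 to 0.3. The rise in power from 73% to between 77% and 87% rests further on d = 0.5, two-sided testing and marginal groups of 54. At the cited 23 mg, power is already so high that only the narrower interval would matter. In a comparison of single cells at d = 0.5, this range of R² would not bring power to 80%. No shortfall against the stated power is established.

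**What to change.** In Data Analysis, before unblinding, replace the primary model with an ANCOVA of 48-hour morphine consumption on preoperative treatment, postoperative treatment, their interaction, surgery type (abdominal or thoracic) and baseline heat pain threshold. Set missing baseline thresholds to the mean so that no patient is lost. Add centre only if there are in fact two, and make the abstract and the methods agree on that. First confirm that heat pain threshold is measured before surgery; if it is not, keep surgery type alone. Retain the unadjusted 2 × 2 ANOVA as a sensitivity analysis.

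The cost is a sentence or two of text and two or three of 104 error degrees of freedom. No patients are added, and no new data if the baseline threshold is collected as the article implies. If the covariates prove unrelated to morphine use, the loss of precision is negligible.

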**Discussion:**

The results of this study will provide information on the analgesic effectiveness of etoricoxib in preemptive analgesia and will give hints on possible preventive effects of persistent pain.

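### The long-term sensitisation aim has no named six-month comparison, and the stated route (significant repeated-measures ANOVA, then Bonferroni t-tests) is weaker than a baseline-adjusted one on the same data

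*Protocol article*

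**What the plan says.** The Data Analysis section gives one method for QST and pain intensity, modelled on the 2 × 2 ANOVA of the primary endpoint: "Secondary outcome measures (QST, pain intensity) will be analysed equivalent, taking into account the test interval (repeated measurement ANOVA". The follow-on step is: "ANOVA will be adjusted according to Bonferroni using t-test for post-hoc confirmation of significant alterations". No time point or model term is singled out.

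The discussion of QST ties a separate question to one time point: "A follow-up sensory testing in our trial is performed six months after intervention", followed by "Therefore, we will be able to provide information regarding long-term sensitisation after surgery, too". The abstract adds, more cautiously, that the results "will give hints on possible preventive effects of persistent pain".

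On treatment, the Interventions section states a preoperative dose on day 0, after which "patients receive either etoricoxib 120 mg p.o. or placebo for the next three postoperative days (day 1-3". It adds for everyone: "All patients will receive standardised morphine (patient controlled analgesia PCA; bolus 2 mg; interval 10 min; max dosage 30 mg/4 h". The Etoricoxib section gives "a t1/2 of approximately 20 hours that enables once-daily dosing". The assessment days stand only in Figure 1, which is not shown in the text available.

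**The concern.** Whether treatment changed long-term sensitisation is a question about the six-month reading, when no study drug remains. The stated analysis covers all readings together and yields an arm effect, a group-by-time interaction and post-hoc t-tests. None of these is named as the answer to the six-month question.

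Two things are at stake:

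- **Power.** A real effect at six months has to pass a global test and then a Bonferroni-split t-test, although one planned comparison would address it directly.
- **Interpretation.** If some readings fall in the first days, they are taken under etoricoxib in the active arms and under self-titrated morphine in all arms. A significant global term could then come from those readings alone.

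**Working it through.** The plan states no power or effect size for QST or pain, so there is no figure of its own to reproduce.

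**Inputs from the article**
- About 60 patients per level of each factor and 10% dropout (section on allocation, blinding and sample size): 60 × 0.90 = 54.
- Alpha 0.05, taken as two-sided because sidedness is not stated.
- Half-life about 20 h; study drug on days 0 to 3.

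**Assumptions**
- Effect 0.6 SD at six months only, unit SD, equal correlation ρ = 0.3 or 0.5 between readings.
- A baseline and a six-month reading, with k = 0 to 3 early readings between them, so T = k + 2 levels.

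**1. Drug remaining.** The fraction is 0.5^(h/20): 0.44 at 24 h, 0.19 at 48 h, 0.03 at 100 h. Any reading on days 1–3 is on drug in the active arms; six months is not.

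**2. Direct six-month test.** 0.6 × √(54/2) = 3.118. Power = Φ(3.118 − 1.96) = Φ(1.158), about 87–88%.

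**3. Baseline-adjusted six-month comparison.** The residual SD is √(1 − ρ²).
- ρ = 0.3: SD 0.954; 3.118/0.954 = 3.268; Φ(1.308) = 90%.
- ρ = 0.5: SD 0.866; 3.118/0.866 = 3.600; Φ(1.640) = 95%.

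**4. Arm effect averaged over time.** The effect shrinks to 0.6/T; the SD of the patient mean is √((1 + (T − 1)ρ)/T).
- T = 2: effect 0.30, SD 0.806 or 0.866, power 49% or 44%.
- T = 5: effect 0.12, SD 0.663 or 0.775, power 15% or 12%.

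**5. Group-by-time interaction.** The noncentrality is (n/2) Σ(v − mean v)²/(1 − ρ), where v holds the effects at each time. Take three early readings plus six months, without baseline as a level. Early-only effects (0.6, 0.6, 0.6, 0) give Σ = 3 × 0.15² + 0.45² = 0.27. A late-only effect (0, 0, 0, 0.6) also gives 0.27. The noncentrality is therefore the same, 10.4 for ρ = 0.3 and 14.6 for ρ = 0.5, with power about 77–91% in both cases. The term shows that arms differ over time, not that they differ at six months. The exception is k = 0: with only baseline and six months, the interaction is the comparison of change from baseline. That does address the question, but with SD √(2(1 − ρ)), hence power 75% or 88%, no better than step 2.

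**6. The stated route.** I simulated 6,000 trials per setting. The gate opens if the arm effect or the interaction is significant at 5%. The six-month t-test must then reach 0.05/T.

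| Early readings k | Gated route, ρ = 0.3 | Gated route, ρ = 0.5 |
|---|---|---|
| 0 | 77% | 79% |
| 1 | 72% | 75% |
| 2 | 68% | 71% |
| 3 | 65% | 67% |

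Simulation error is about one percentage point; repeat runs put the range at about 64–79%. In the same runs the direct test found the effect in 86–88% and the baseline-adjusted comparison in 89–95%.

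**7. Sensitivity.**
- If the Bonferroni split covers only readings after baseline, the gated route finds 67–85%, still below the direct test.
- If only the arm effect opens the gate, it finds 12–48%.
- With a 0.5 SD effect, the direct test has 74% and the baseline-adjusted comparison 78–85%. A t-test split over 2 to 5 time points has 64% down to 51%, even before the gate.

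**The case against.** The strongest reply is that the plan does not pool anything. It makes the test interval a factor, so the ANOVA contains a group-by-time term, and the post-hoc t-tests can compare arms at single times. This stands. A reader might infer that a true six-month effect would usually be missed. The documents do not support that: the low powers in step 4 apply only if the averaged arm effect is read alone, while the interaction has about 75–91% power for a late-only effect.

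A reader might also infer that ordinary analgesia on days 1–3 will pass for prevented sensitisation. The text does not establish this either. It does not say that QST is done in the first days, nor that pain is rated at six months. It ties the long-term aim to the six-month QST reading itself and speaks only of hints on prevention. The confusion needs early readings to exist and the arm effect to be read as the answer. With one to three early readings and baseline as a level, a 0.6 SD early-only effect makes the arm effect significant in 23–79% of simulated trials, but the gated six-month t-test is then falsely positive in only 1–2%.

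A third reply is that the split buys stricter error control. It does, but a single comparison named in advance holds 5% without it.

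Last, a condensed article may leave secondary contrasts to a fuller plan. That limits the weight of the point. It does not remove it, because the article states a model and a confirmation step, and that stated route is what is weaker.

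**Conclusion.** The point holds as a cheap improvement to a secondary analysis, not as an error that threatens the trial. For the six-month question, the stated route finds a 0.6 SD effect in about 64–79% of trials, against about 87% for a direct test and about 90–95% with baseline adjustment. These figures rest on the assumed effect, correlation and number of readings, and on reading the post-hoc rule as a gate followed by a split over all time points. The ordering persists under the alternatives in step 7; the size of the gap does not. The interpretive risk is conditional on a schedule that cannot be seen.

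**What to change.** In the Data Analysis section:

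- For the long-term sensitisation aim, name the six-month QST value as the estimate, and six-month pain if it is collected. Compare it by the preoperative and by the postoperative factor.
- Adjust for the preoperative value as a covariate, not as a level of the repeated factor.
- Keep the repeated-measures ANOVA to describe the time course.
- Report any readings from the day 0–3 treatment period as acute effects on treatment, not as evidence on prevention. Align the discussion of QST with this.

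The cost is wording and one model per outcome, with no new data or patients. The downside is that early results support a narrower claim. Multiplicity across the many QST measures is untouched by this change and remains under either approach.
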